### Randomisation

Patients will be randomised using a block randomisation programme that will assign to either lung and IVC ultrasound-guided decongestion therapy (‘intervention group’) or clinical-guided decongestion therapy (‘control group’). Randomisation will be stratified by age (<70 or >70 years) and by left ventricular function (<50% or >50%). Randomisation will be performed within 24 hours after hospital admission using the REDCap randomisation module with a 1:1 allocation scheme.

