**Figure 2 F2:**
[figure not shown]
Therapeutic algorithm. Adapted from: Mullens *et al*
35 and Hollenberg *et al*.^36^ BP, blood pressure; CAVAL US, inferior vena cava and lung ultrasound; IV, intravenous; LCOS, low cardiac output syndrome; UO, urinary output.

All the patients will undergo lung and IVC ultrasound, independently of the group assigned during randomisation. Furthermore, an echocardiogram will be performed within 48 hours from admission according to the recommendations,^15^ as part of our standard of care.

A checklist will be made prior to hospital discharge to assess compliance with guideline-based treatment, vaccination, counselling and medical appointment after discharge. All patients will receive education by an HF nurse, who will provide educational material and drug treatment indications in a written grid.

Patients will be randomised into two arms and will be blinded to the assigned arm:

Control group: the treating medical team will be blinded to the lung and IVC ultrasound results. Patients will receive the standard of care of our centre and titration of diuretics will be based on standard practices (physical examination, symptoms and results of laboratory tests). The therapeutic goal (see figure 2) will be to discharge patients with relief of signs and symptoms of congestive HF, without ECG changes or abnormal laboratory findings that contraindicate hospital discharge. Circulating biomarkers of congestion are not part of the standard of care.Intervention group: the treating medical team will be unblinded to the lung and IVC ultrasound results. Patients will receive treatment for decongestion according to the results of the intervention plus the standard care (figure 2). The therapeutic objectives will be similar to the control group, with relief of the signs and symptoms of HF and additionally without congestion or mild residual congestion in the ultrasound test. At the discretion of the treating physician, the patient may be discharged when he or she shows mild to moderate signs of congestion in improvement with oral diuretics for more than 24 hours with adequate diuretic response.

Both groups will be scheduled to follow-up visits in our ambulatory clinic 7–10 days after discharge, and at least once per month.

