### Statistical analysis plan

According to our preliminary pilot data derived from a sample of 20 patients during the new ultrasound tool proof trial, 70% had >5 B-lines and/or dilated IVC at discharge with the usual care strategy at our hospital. Therefore, to reach a relative risk reduction of 50% (ie, 70% in usual care and 35% in the CAVAL US-guided strategy), setting a power of 80% and a two-sided type I error rate of 5%, we will need 29 patients in each arm to accomplish our hypothesis.

Analysis will be performed by intention to treat. Continuous variables will be expressed as mean and SD, or median and IQR, according to their distribution. Normality of distribution of variables will be assessed using the Kolmogorov-Smirnov test or the Shapiro-Wilk test, according to the sample size. Continuous variables will be compared using the Student’s t-test or the Mann-Whitney U test, as applicable. Categorical variables will be presented as numbers and percentages. The Χ^2^ test or Fisher’s exact test will be used to compare proportions. No imputation will be made for missing data.

The Kaplan-Meier method will be used to analyse time-to-first event data. The differences in time-to-event distributions will be evaluated using the log-rank test. Univariate HRs with associated 95% CIs will be estimated for the composite primary endpoint and secondary endpoints and derived from the Cox proportional-hazards model; however, multivariate Cox regression analysis will only be used if there are important prognostic factors or patients’ baseline characteristics exhibiting significant imbalance between the two groups established by randomisation. In all cases, the alpha error will be set at 5% to establish statistical significance. All the statistical calculations will be performed using SPSS V.24 software package.

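### Randomisation is stratified by age and LVEF but the stated analyses are not, and the Cox model is adjusted only after an observed baseline imbalance

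*Protocol article*

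**What the plan says.** Under Randomisation, the protocol article states: "Randomisation will be stratified by age (<70 or >70 years) and by left ventricular function (<50% or >50"%). Allocation is made within 24 hours of admission, "using the REDCap randomisation module with a 1:1 allocation scheme".

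Under Statistical analysis plan, proportions are compared by chi-square or Fisher's exact test. Time-to-event data are compared by Kaplan-Meier curves and a log-rank test, with univariate hazard ratios from a Cox model. None of these carries the stratification factors. Adjustment is conditional: "multivariate Cox regression analysis will only be used if there are important prognostic factors", or baseline characteristics, "exhibiting significant imbalance between the two groups established by randomisation". No covariates are listed, no criterion specific to imbalance is given, and the text does not say whether the adjusted or the unadjusted result is then the main one.

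Age and LVEF return only under Subgroup analysis, where they define subgroups for the primary endpoint. That does not adjust the overall treatment comparison.

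On timing, the Study intervention section says that "an echocardiogram will be performed within 48 hours from admission", as part of standard care.

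**The concern.** Two separate things are wrong, and they affect different endpoints.

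**The strata are ignored.** Stratified randomisation makes the arms more alike on the stratified factors than simple randomisation would. An analysis that leaves those factors out uses a variance that is too large whenever they predict the outcome. The test is then conservative and some power is lost. This applies to the primary endpoint and to the 90-day outcomes.

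**Adjustment waits for an imbalance.** After proper randomisation, a baseline difference is due to chance, so its statistical significance says little about whether the covariate matters. In a trial of 58 patients an important covariate can be out of balance without reaching significance, and an unimportant one can reach it. The rule also decides the model after the data are seen and names no main result, so the reported hazard ratio could be either of two. Because it refers to Cox regression only, it bears on the 90-day outcomes and offers no adjusted analysis of the binary primary endpoint.

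These are rules that the article states, not details that it leaves to a fuller document.

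**Working it through.** **1. The plan's own figure.** Inputs from the Statistical analysis plan section: "70% in usual care and 35% in the CAVAL US-guided strategy", 80% power, two-sided 5%. With unpooled variance, n per arm = (z₀.₉₇₅ + z₀.₈₀)² × [p₁(1−p₁) + p₂(1−p₂)] / (p₁−p₂)² = 7.849 × (0.21 + 0.2275) / 0.35² = 28.03, rounded up to 29. The stated 29 per arm is reproduced. It rests on an unadjusted comparison. Exact enumeration at 29 per arm gives 77.4% power for the uncorrected chi-square test, so there is little to spare.

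**2. Cost of ignoring the strata (primary endpoint).** The documents do not say how strongly age or LVEF predicts congestion at discharge, so a range is assumed. Setting: 58 patients, four equal strata, permuted blocks of 4 (block size and stratum shares are assumptions), the same odds ratio (OR) for each factor, 20,000 simulated trials per setting. Marginal rates are 70% and 35% for power, and equal in both arms for type I error. The unadjusted chi-square test is compared with the Cochran-Mantel-Haenszel (CMH) test over the four strata, each at the nominal 5%.

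| OR per factor | Type I error, unadjusted | Type I error, CMH | Power, unadjusted | Power, CMH | Gain (points) |
|---|---|---|---|---|---|
| 1 | 5.1% | 5.1% | 77.8% | 78.0% | 0.2 |
| 1.5 | 4.7% | 5.0% | 78.0% | 78.5% | 0.5 |
| 2 | 4.2% | 4.9% | 78.4% | 79.7% | 1.3 |
| 3 | 3.7% | 4.7% | 78.4% | 81.7% | 3.3 |

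The rows combine separate runs. Repeat runs put the gain at 0.4–0.6, 1.2–1.5 and 3.1–3.4 points for OR 1.5, 2 and 3, and the unadjusted type I error within a few tenths of a point of the table. With unequal strata (assumed prevalences 75% and 35%) the gains are 0.3, 1.0 and 2.6 points. The simulated 77.8% at OR 1 agrees with the exact 77.4% in step 1.

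**3. Can the trigger reach the stratification factors?** With blocks of 4, each stratum can be off balance by at most two patients. Take a bad case with near-equal strata: 17 v 13 patients in one level of a factor and 12 v 16 in the other. Chi-square = 58 × (17×16 − 13×12)² / (29 × 29 × 30 × 28) = 780,448 / 706,440 = 1.10, far below 3.84. In the simulations neither dichotomised factor ever showed a significant imbalance.

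**4. How often would the trigger fire by chance?** If k independent baseline variables were each tested at 5%, the chance of at least one significant result is 1 − 0.95ᵏ: 23% for k = 5, 40% for k = 10, 64% for k = 20. The documents give no k and name no baseline test, so this is illustration only.

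**5. Events available for a stratified Cox model.** The Introduction gives 25–30% readmission within 90 days. For 58 patients that is 0.25 × 58 = 14.5 to 0.30 × 58 = 17.4 events, or about 4 per stratum. The composite is wider than readmission, so the true count may be higher.

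**6. The stratum definitions.** The Randomisation section's cuts leave age exactly 70 and LVEF exactly 50% unassigned. The Subgroup analysis section repeats the age gap, but its LVEF wording places 50% in the upper group. Randomisation is due by 24 hours and the echocardiogram by 48 hours, and the article does not say which LVEF value is used to stratify.

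**The case against.** An unadjusted test after stratified randomisation is valid. Its error is in the safe direction, and at OR 1.5 to 2 the gain from stratifying is about one point of power. This stands: a stratified primary analysis is an efficiency gain that needs no extra patients, not the repair of an invalid test. A reader might infer an inflated false-positive risk, but step 2 shows the opposite.

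A reader might also infer that the trigger leaves the primary result open, since the analysis section speaks of hazard ratios for a composite that it calls primary. The documents do not support that. Under Study endpoints and follow-up, the primary endpoint is a yes/no status at discharge and the event composite is secondary. The label should be corrected, but the rule concerns Cox models only.

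The text names no significance test for imbalance. Reading it as one is an inference, though a plausible one because the same paragraph sets alpha at 5% in all cases. It would also be too strong to say that the factors could never trigger adjustment: another block size, strongly unequal strata, or age compared as a continuous variable could still show a difference.

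Calling the strata defective goes too far. The missing equality signs are a drafting slip, and 48 hours is an upper limit for the echocardiogram, so LVEF may well be known at randomisation. Finally, training is described as done before the trial began, so enrolment may have started; changing the strata midway, or adding a new LVEF estimate, would carry a cost.

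**Conclusion.** The point holds in a limited form. The stated analyses ignore the stratification. The imbalance trigger is a poor rule at any prognostic strength, because it selects covariates by chance differences and leaves the main Cox result unnamed. Its reach is the 90-day outcomes.

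For the primary endpoint the harm is conservatism of the modest size shown in the table. It depends on prognostic strengths that the documents do not give, and on assumed blocks of 4 and equal strata. If neither factor is prognostic, stratifying costs nothing visible, so there is no case against it. The gaps in the cuts and the 24-hour and 48-hour limits call for clarification only. The change should be made, but the trial's validity does not hang on it.

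**What to change.** - **Trigger:** delete it, or keep it as a labelled sensitivity analysis.
- **Primary endpoint:** prespecify a Cochran-Mantel-Haenszel test, with a Mantel-Haenszel risk difference and risk ratio, over the four randomisation strata.
- **90-day composite:** prespecify a Cox model with age group and LVEF group as covariates as the main analysis. With so few expected events this is preferable to stratifying four ways.
- **Unadjusted results:** report for both endpoints as sensitivity analyses.
- **Strata:** write the cuts without gaps and identically under Randomisation and Subgroup analysis (<70 / ≥70 years, <50% / ≥50%). State which already available LVEF value is used at randomisation. Analyse by the strata as recorded at randomisation.

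The cost is wording in the analysis, randomisation and subgroup sections. The sample size need not change, and no new measurement is needed. Because the analysis uses the strata as recorded, patients already enrolled need not be restratified.

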### Confidentiality

The investigators and the Institutional Review Board of Instituto Cardiovascular de Buenos Aires will implement measures to protect the confidentiality of all the information according to the Argentine personal data protection law 25.326. These records will be kept confidential. The participants will only be identified by using numbers or letters as identification code. The identity of the participants will not be revealed if the results of the study are published.

## Discussion

Residual congestion at hospital discharge is one of the major factors contributing to readmission for HF,^13 41^ even in patients without clinical signs of congestion,^42^ possibly due to the persistence of subclinical overload.

Since the advent of LUS, we have gained a broader notion of the sequence of events leading to pulmonary oedema starting with increase in left ventricle end-diastolic pressure that translates into an increased pulmonary capillary wedge pressure. This phenomenon is called haemodynamic congestion and is the initial cause to break the Starling’s equilibrium in the alveolar–capillary barrier, resulting in lung fluid overload.^43^ The intermediate event between haemodynamic and clinical pulmonary congestion is subclinical pulmonary congestion, detectable by LUS as multiple B-lines.^44^ Clinical congestion becomes evident hours, days or weeks later.

Detection, dynamic monitoring, and management of clinical and subclinical congestion could help improve prognosis, especially during the vulnerable period following hospitalisation for AHF. The assessment of pulmonary congestion by LUS and of systemic congestion in the IVC with a standardised quantitative approach could represent a valuable and novel tool to guide the management of these patients.

Among the limitations of our proposed study, the fact that it will be performed in a high-complexity single centre dedicated to cardiovascular diseases could hamper the generalisation of the results. Nevertheless, the broad inclusion criteria established and the simplicity of the CAVAL US protocol indicate that this ultrasound-guided treatment strategy could be applied in centres of less complexity. Second, the treating physicians responsible for treatment decisions are experienced cardiologists working in a multidisciplinary programme composed by a specialised nurse. This could reduce the number of events in both groups, reducing not only the power of the trial, but also the potential benefits of ultrasound-guided therapy by improving the evaluation in the control group due to the high expertise of the professionals. Nevertheless, we have proposed an algorithm for standardised care that will allow reproducibility of treatment in other centres.

The therapeutic algorithm was adapted from the two most recent consensus statements published by the Heart Failure Association of the European Society of Cardiology^35^ and the American College of Cardiology,^36^ which have not been yet validated but were based on experts’ opinion. Further, in the suggested daily evaluation of congestion, in the CAVAL US-guided therapy arm, the clinical assessment is complemented by ultrasound findings to detect subclinical abnormalities.

The treating medical team will be blinded to the results of the ultrasound of the control group and the patients will be blinded to the arm assigned as a consequence of the nature of the study. Furthermore, while there is no way to blind the patient’s clinical status to the team performing the ultrasound examinations, all the ultrasounds will be interpreted and reported by a Core Lab, made up of two expert sonographers, blinded to the clinical characteristics of the patient.

The evaluation of congestion is extremely difficult, especially when a binary definition, such as present or absent, is required. Clinical scores combining several clinical indicators have proven to better assess the level of congestion than any independent indicator.^44^ Recognising that there are many indicators of pulmonary congestion, we focused on a comprehensive assessment of clinical congestion by means of the EVEREST risk score.^45^

Lung and IVC ultrasound are simple techniques; one morning hands-on experience or even a standardised internet-based module of 2 hours is sufficient to achieve excellent reproducibility in identification and quantification of B-lines, even among LUS-naive sonographers.^46^ The operators will attend a theory course and two workshops to practise the technique, standardise the way the examination is conducted and improve correlation between those who interpret the images.

To date, neither the international evidence-based recommendations nor the expert consensus document for quantification of pulmonary congestion by LUS in HF has recommended how to quantify B-lines in each intercostal space.^39 46^ Therefore, the method of counting B-lines noted in the intercostal space at any instant was chosen, since it is technically simpler to perform and more reliable than the other methods previously reported.^47^ In addition, and opposed to previous publications,^22 24^ longer LUS clips will be recorded in each lung zone since the number of B-lines that can be detected with longer clips in patients with HF is greater.^48 49^

It is worth mentioning that several approaches have been proposed to estimate the volume and severity of pleural effusion.^50–52^ However, their value in patients with AHF may be limited. This is because some of these techniques require several measurements that are time-consuming, while others can only be applied for moderate to large effusions, as they were primarily developed to predict safety of thoracentesis. A semiquantitative score for pleural effusion in patients with AHF has been recently suggested.^40^

Finally, lung and IVC ultrasound is a simple, non-invasive technique that does not require the use of Doppler or complex methods of quantification, is inexpensive and can be performed with a hand-held device that can be easily sanitised. This is an extremely important aspect considering that the trial will be conducted during the COVID-19 pandemic.

## Conclusion

The CAVAL US-AHF clinical trial will provide evidence on the usefulness of this innovative ultrasound protocol that evaluates both right-sided congestion through the evaluation of the IVC and left-sided congestion through LUS to guide pulmonary decongestion in patients hospitalised for AHF.

## Data Availability

Data are available upon reasonable request.
